## Methods

### Study design

This Hybrid Type 2 Effectiveness-Implementation trial will use a cluster-randomized modified stepped-wedge design (see Fig. 1). Nine CSC sites throughout the USA, in both rural and urban regions, will be randomized to one of three start dates (waves) [46, 47]. Each site will recruit participant dyads, comprised of family member/support persons and clients with FEP enrolled in CSC, with separate cohorts of participant dyads recruited into the ACC and FAMES conditions. Aim 1 (effectiveness) seeks to evaluate whether integrating FAMES improves family engagement in CSC compared to ACC. In Aim 2 (mechanisms of change), we will use quantitative survey data to examine whether our theoretically driven target mechanisms of connectedness, self-efficacy, and motivation mediate FAMES engagement. Aim 3 (reach, adoption, implementation, and maintenance) will use a concurrent (quan + QUAL) mixed methods approach to evaluate implementation through an equity-focused lens. This study follows the Standard Protocol Items: Recommendations for Interventional Trials (SPIRIT) reporting guidelines (see Additional file 1 in the supplementary materials for the SPIRIT checklist) [48].

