### Data collection procedures

Family members in the ACC and FAMES conditions will complete quantitative assessments at baseline, months 1–3, and at follow-up (3 months post-intervention), whereas client participants will complete assessments at baseline, month 3, and at follow-up. Figure 3 displays the SPIRIT diagram outlining the schedule of measures across the study period. All assessments will be collected by research staff over the phone and entered directly into REDCap. For participants who prefer to complete assessments on their own, SMS or link-to-text survey features in REDCap will be enabled to capture responses. For completing all assessments, family member/support person participants will receive a total of $275 and client participants will receive a total of $110.

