**Other indicators (to be used as covariates/independent variables in analyses if Aims 1–2)**			
*Individual characteristics*	**Family member and client characteristics** will be assessed using modules from the *PhenX Toolkit Social Determinants of Health Core and social determinants of health*. Age, gender identity, sex, race, ethnicity, education, employment, marital status, religious preference, health insurance, etc	Family & client participant survey	BL
*Contextual factors*	**Contextual factors** will be assessed using the *Citizenship Measure* is a 46-item that measures community connectedness and engagement [70]	Family participant survey	BL
*Program characteristics*	**Program characteristics** will include setting, location, # of team members	Provider survey	BL

*BL *baseline, *PRE *pre-implementation phase, *FU *3-month post follow-up

Implementation outcomes are guided by the extension Reach, Effectiveness, Adoption, Implementation, Maintenance/Sustainability (RE-AIM) extension framework which identifies indicators related to sustainability and health equity-related considerations for tracking each domain of RE-AIM [71–74]. Table 2 outlines all measures to capture implementation outcomes which will be completed by family peers and CSC providers (i.e., family peers, program directors, and family education and support providers). Research staff will email participating CSC providers a unique REDCap link to complete pre- and post-training surveys during the pre-implementation phase. A longitudinal qualitative research approach will be used to explore potential barriers and facilitators to delivery and engagement that may inform modifications to implementation over time and understand experiences over time during the active implementation phase [77–79]. Semi-structured qualitative interviews will be scheduled and conducted via videoconference (i.e., Zoom) with family peers at baseline (end of pre-implementation phase) and at 6, 12, and 24 months after the commencement of the active implementation phase. Interviews will also be conducted with family education and support providers and/or program directors at baseline and at 12 and 24 months after the commencement of the active implementation phase. All interviews will be audio recorded, transcribed verbatim, and reviewed for accuracy.

**Table 2 Tab2:** Implementation outcomes: study assessments

Construct	Measure	Data source	Timepoint

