#### Aim 1: Impact of FAMES on primary and secondary outcomes

##### Quantitative data analysis

Statistical analyses for primary engagement outcomes will use Generalized Linear Mixed Models (GLMM) to compare engagement rates between the control (ACC) and intervention (FAMES), with a random effect for cluster (site), a fixed effect for each phase (ACC and FAMES), and a fixed effect for implementation wave to control potential time-related confounding [80, 81]. GLMM will also be used to assess change scores on secondary outcomes for family member and client participants from baseline to 3 months. Restricted maximum likelihood estimation with Kenward-Roger standard error and degrees of freedom correction to accommodate for our relatively small number of clusters will be used. Supplemental analyses will assess the likelihood of including relevant individual and program covariates (e.g., age, biological sex, race, and others) in models if significant differences among covariates occur between ACC and FAMES samples. Analysis of the secondary outcomes collected only from FAMES participants at follow-up will employ GLMMs to compare baseline to 3-month to follow-up inventory scores as a random effect repeated measures factor. Fixed effect covariates (e.g., age, biological sex, race, and others) will be included in these models as appropriate. A Bonferroni correction will be applied to primary engagement outcomes (first session attendance and total attendance per family and client) to control for multiple testing.

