### Power analysis

All power analyses were conducted with G*Power v. 3.1 [87], using different potential sample and effect sizes, assuming nine CSC sites, and three waves to estimate the power to detect effects. Power estimations for Aim 1 focused on engagement primary outcomes. Using the design effect approach in the Shiny-CRT power estimation application [88], a sample size of 450 participants, with an effect size of 0.5, at a 2-sided alpha level of 0.025, and assuming an ICC in each period of 0.01, the estimated power to detect a significant difference between ACC and FAMES conditions for the primary outcome of engagement would exceed 85%. For specific to Aim 2, power analyses assumed a conservative *R*^2^ value of 0.10 for predicting engagement from seven Block 1 control variables. Based on a sample of 225 family member participants in the FAMES condition, at a two-sided alpha level of 0.05, estimated power would be 98% when assessing whether *R*^2^ differed significantly from zero. With the addition of three Block 2 mediator variables (change in inventory scores), if *R*^2^ was to increase to 0.20 so that the change in *R*^2^ is 0.10, with an adjustment to the two-sided alpha to 0.025 due to multiple hypothesis tests and potential correlation between Block 1 and 2 predictors, and an adjusted effect size for Block 2 change given Block 1 variables [89] power would increase to 99% to detect a significant change in *R*^2^. Estimated power to achieve significant differences in implementation outcomes (i.e., pre- and post-change in knowledge) assumed a standardized mean difference of 0.60. Based on a sample of 20 family peer and provider participants, at a one-sided alpha level of 0.05, and a correlation among repeated measures of 0.50, estimated power would be 83% to establish significant change in knowledge. As such, this study is sufficiently powered (> 80% power) to detect meaningful differences in engagement outcomes, mediation effects, and knowledge, with adjustments for clustering and the stepped-wedge design structure.

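### Secondary survey outcomes are compared as change scores with no baseline covariate named, and covariates enter the supplemental ACC–FAMES models only after a significance test

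*Protocol article*

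**What the plan says.** In the protocol article, the Aim 1 part of the Data analysis plan states "GLMM will also be used to assess change scores on secondary outcomes for family member and client participants from baseline to 3 months". It mentions no baseline-score term. On other covariates it says "Supplemental analyses will assess the likelihood of including relevant individual and program covariates", and these enter "in models if significant differences among covariates occur between ACC and FAMES samples". The examples are age, biological sex and race, and the list is left open.

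The models that use follow-up data from FAMES participants alone have a different rule: "Fixed effect covariates (e.g., age, biological sex, race, and others) will be included in these models as appropriate". That rule names no significance test, but it fixes no list either.

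Table 1 schedules perceived stress, GAD-7, PHQ-9 and CAPE-P15 at baseline, 3 months and follow-up. The Data collection procedures agree for clients: "whereas client participants will complete assessments at baseline, month 3, and at follow-up". Table 1 also lists individual, contextual and program characteristics under a row that reads "to be used as covariates/independent variables in analyses if Aims" 1–2, without saying which of them go into a model.

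The Study design section describes sites recruiting dyads "with separate cohorts of participant dyads recruited into the ACC and FAMES conditions". Sites are randomized to waves; participants are not individually randomized. The main engagement model has fixed content: a random site effect, a fixed phase effect and a fixed wave effect.

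**The concern.** There are two separate choices here, and the article states both of them; neither is simply left open.

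First, a change score subtracts the baseline with its slope fixed at 1. When the correlation between baseline and 3 months is below 1, that slope is too steep and adds noise to the ACC–FAMES comparison. The loss falls on the family and client symptom outcomes, for which the article states no power.

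Second, testing each covariate for a difference between the two samples asks whether it is imbalanced, not whether it predicts outcome. A strong predictor with moderate imbalance is left out, while a weak one with a chance imbalance is let in. The resulting model depends on the data. The article's own Background says that ethnoracially minoritized and low-income families are less often involved in CSC, so it already identifies prognostic factors for engagement. Yet race enters an Aim 1 model only if it passes the test. Aim 2, by contrast, names its demographic block in advance.

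**Working it through.** **The plan's own figure.** The only Aim 1 power figure is for engagement: above 85% with "a sample size of 450 participants", effect size 0.5, two-sided alpha 0.025 and ICC 0.01. Under an assumed layout of 3 sequences by 4 periods, with 3 sites per sequence and 450/36 = 12.5 participants per site-period, the standard stepped-wedge variance gives SE 0.1505. Power is then Φ(0.5/0.1505 − 2.241) = Φ(1.08) = 86.0%. The figure can therefore be reproduced under that layout, but it concerns a different outcome and does not depend on this point.

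**Precision.** Inputs: 225 dyads per condition (article), alpha 0.05 (article), and equal SDs at both times, set to 1 (assumed). The only repeated-measures correlation in the article, 0.50, belongs to the provider knowledge test, so a range of r is used.

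- Variance of a change score: 2(1 − r).
- Variance of a baseline-adjusted score: 1 − r².
- Ratio: (1 − r²)/[2(1 − r)] = (1 + r)/2.
- With unequal SDs σ₀ and σ₁, the change score exceeds the adjusted score by (σ₀ − rσ₁)², which is never negative.

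| r (assumed) | Change | Adjusted | Ratio | Adjusted power where change score has 80% |
|---|---|---|---|---|
| 0.3 | 1.40 | 0.91 | 0.65 | 93.5% |
| 0.5 | 1.00 | 0.75 | 0.75 | 89.9% |
| 0.7 | 0.60 | 0.51 | 0.85 | 86.0% |
| 0.8 | 0.40 | 0.36 | 0.90 | 84.0% |

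At r = 0.5 the gain equals a sample 1/0.75 = 1.33 times as large. As an illustration, take a true effect of 0.25 SD and a design effect of 1 + (25 − 1) × 0.01 = 1.24, with 225/9 = 25 per site and phase; both are assumptions. Power with change scores against adjusted scores is then 52% and 70% at r = 0.3, 66% and 79% at r = 0.5, and 87% and 92% at r = 0.7.

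**Baseline imbalance.** Suppose FAMES starts 0.2 SD higher.

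- If the difference is chance, the change-score estimate shifts by −(1 − r) × 0.2, which is −0.14, −0.10 and −0.06 SD at r = 0.3, 0.5 and 0.7. The adjusted estimate does not shift.
- If the cohorts differ stably and would change in parallel, the change score is unbiased. The adjusted estimate is then off by (1 − r) × 0.2, the same sizes with the opposite sign.

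**The screen.** Ignoring clustering, the SE of a standardized covariate difference is √(2/225) = 0.0943. An observed imbalance below 1.96 × 0.0943 = 0.185 SD never passes. A true difference of 0.15 SD is missed with probability about 1 − Φ(0.15/0.0943 − 1.96) = 1 − Φ(−0.37) = 64%.

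**Both together.** A simulation used 4,000 replicates, 9 sites with 25 per phase, and one covariate with assumed coefficient 0.4. The SDs of the estimated effect were:

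| r | Change, test-selected covariate | Change, prespecified covariate | Baseline-adjusted, prespecified covariate |
|---|---|---|---|
| 0.3 | 0.1127 | 0.1068 | 0.0836 |
| 0.5 | 0.0916 | 0.0855 | 0.0717 |
| 0.7 | 0.0696 | 0.0626 | 0.0553 |

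The last column has 0.55, 0.61 and 0.63 times the variance of the first. Removing the screen alone, column two against column one, gives (0.1068/0.1127)² = 0.90, then 0.87 and 0.81. All estimators averaged about zero under no effect, so in this setting the gain is in precision.

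**The case against.** **Bias.** A reader might infer that baseline adjustment is less biased in general. The documents do not support that. ACC and FAMES are successive cohorts: with 18 months of ACC recruitment, 3 months of pre-implementation and 30 months of FAMES, two participants at one site may enter anywhere from about 3 to 51 months apart. A real shift in case mix is possible, and which method is then less biased rests on assumptions that the data cannot check. This objection stands. It is the reason to keep the change score as a sensitivity analysis.

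**Status of the screened models.** A reader might also infer that the screen makes the main analysis data-driven and voids its p-values. The article labels these analyses supplemental, and the main engagement model has fixed terms. The criticism therefore reaches the supplemental ACC–FAMES models only.

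**Left to the analysis plan.** The article may be condensed, and it does not say that the baseline score is excluded. A change-score model that also contained the baseline score would give the same treatment effect as the adjusted model. This carries some weight for the baseline term. It does not rescue the covariate rule, which is stated outright. Nor does it alter the fact that the method as written is the less efficient one.

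**Reach.** Client attendance comes from administrative data and has no scheduled baseline score, so baseline adjustment does not apply to it. The follow-up models for FAMES participants do not use the significance rule.

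**Conclusion.** The point holds as one of efficiency and prespecification. For the four survey scales, the stated change-score analysis has a larger variance than a baseline-adjusted analysis of the same data. The loss corresponds to 35%, 25%, 15% and 10% of the sample at r = 0.3, 0.5, 0.7 and 0.8. Those correlations and equal SDs are assumptions; the direction holds for every r below 1. Protection against bias is limited to chance imbalance. The significance screen is a poor rule for the supplemental models because it ignores prognostic value and leaves their content to the data. The simulated figures also depend on the assumed covariate strength. The primary engagement result and its stated power are not put in doubt.

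**What to change.** For perceived stress, GAD-7, PHQ-9 and CAPE-P15, make the 3-month score with its own baseline score as covariate the main ACC–FAMES model, keeping the planned site, phase and wave terms. Report the change score as a sensitivity analysis, with a sentence saying that the two answer differently if the cohorts differ stably at baseline.

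Delete the rule that ties covariate entry to a significant difference. Replace it with a short list, fixed before outcome data are examined, of mainly individual-level prognostic covariates already collected at baseline, such as age, sex and race/ethnicity. Keep program-level terms few, because only nine sites inform them.

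The cost is a wording change, a few degrees of freedom and a stated method for missing covariates. The baseline score adds no new missing-data burden, because a change score already needs it. No further data collection is required.

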### Family member and client participant dyads

A total of 450 participant dyads will be recruited across nine CSC programs, with 225 participant dyads to receive the ACC and 225 to receive FAMES. Each participant dyad will include a family member and a loved one enrolled in CSC for FEP. Family member inclusion criteria are as follows: (1) one family member/support person of a client enrolled in CSC for ≤ 6 months; (2) ≥ 18 years of age; and (3) during the active implementation phase, did not participate in the ACC. Client inclusion criteria include the following: (1) ≥ 15 years of age, and (2) enrolled in CSC for ≤ 6 months. Potential participants will be excluded if they do not understand the consent and assent process, and if they are non-English or non-Spanish speaking adults or youth.

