**Fig. 3 Fig3:**
[figure not shown]
SPIRIT diagram: schedule of enrollment, interventions, and assessments

Table 1 provides a description of all study measures completed by participant dyads to assess primary and secondary outcomes and mechanisms of change. Measures with accessible versions in the Spanish language will be used, and if not, will be translated into Spanish.

**Table 1 Tab1:** Effectiveness outcomes: study assessments for primary, secondary, and mechanisms

Construct	Measure	Data Source	Timepoint
*Primary outcome*	**Engagement in CSC Family Psychoeducation (Aim 1)** will be measured as first session attendance rate and total attendance rate per family	Administrative data	Monthly
	**Engagement in FAMES (Aim 2)** will be measured by FAMES session attendance rate and the total number of contact minutes with participants by videoconference, in-person, and phone, and # of encounters by email, and text	Family peer survey	Weekly
*Secondary family outcomes*	**Perceived Stress (Aim 1)** will be assessed using the *Perceived Stress Scale*, which contains 10 Likert-style items to assess the degree to which an individual appraises life as stressful	Family participant survey	BL, 3 m, FU
	**Anxiety (Aim 1)** will be assessed using the *General Anxiety Disorder-7 item* [64]*.* Scores 8 or greater is cut-off for anxiety disorder	Family and client participant survey	BL, 3 m, FU
*Secondary client outcomes*	**Client Engagement in CSC (Aim 1)** will be measured as the client attendance rate in CSC	Administrative data	Monthly
	**Depression (Aim 1)** will be measured using the *Patient Health Questionnaire-9 item* [65]. A score of 10 or greater is cut-off for depression	Client participant survey	BL, 3 m, FU
	**Psychosis (Aim 1)** will be measured using *Community Assessment of Psychic Experiences – Positive 15-items Scale* [66]	Client participant survey	BL, 3 m, FU
*Mechanisms*	**Self-Efficacy (Aim 2)** will be measured using the 10-item *General Self-Efficacy scale* [67]. Scores range from 10 to 40, with higher scores indicating greater self-efficacy	Family participant survey	BL, Monthly
	**Connectedness (Aim 2)** will be assessed using the *Social Connectedness subscale of YSS-F* [68, 69], which assesses social support. Scores range from 4–20 where higher scores indicate greater social connectedness	Family participant survey	BL, Monthly

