### Data analysis plan

All analyses will follow an intention-to-treat principle with participant data within clusters analyzed according to the cluster’s randomized crossover time. All quantitative analyses will utilize a type I error rate of *p* < 0.05. Multiple imputation will be used for missing secondary psychological outcomes, with separate imputations conducted by study phase and clinic, incorporating demographic variables to ensure the accuracy of imputed values under the assumption of missing at random. Analyses will be conducted using STATA version 14.2, R statistical software, or the Statistical Package for the Social Sciences (SPSS, version 31.0).

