#### Aim 3: Explore implementation outcomes using mixed methods

##### Quantitative data analysis

All implementation outcomes will be analyzed using GLMM to account for clinic- and provider-level clustering and repeated measurements over time. The models will include random effects for sites and providers and fixed effects for time (such as monthly changes in reach and adoption). Since provider characteristics such as gender, race, and education may influence implementation, they will be included in models if they improve accuracy, as assessed by Akaike Information Criterion (AIC) and Bayesian Information Criterion (BIC). Because some providers may drop out or miss assessments, multiple imputation (MI) will be used to estimate missing data, ensuring unbiased results.

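### The FAMES-only follow-up model declares occasion a random effect, so as written it gives no fixed-effect estimate or confidence interval for change between baseline, 3 months and follow-up

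*Protocol article*

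**What the plan says.** The text is in the protocol article, Data analysis plan, Aim 1, Quantitative data analysis. It introduces the analysis with "Analysis of the secondary outcomes collected only from FAMES participants at follow-up will employ GLMMs" and says these models will "compare baseline to 3-month to follow-up inventory scores as a random effect repeated measures factor". The next sentence gives the fixed part: "Fixed effect covariates (e.g., age, biological sex, race, and others) will be included in these models as appropriate". It states no fixed effect for time and no random effect for participant.

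Two other models in the article assign these roles explicitly:

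- The primary engagement model, in the same paragraph, is specified "with a random effect for cluster (site), a fixed effect for each phase (ACC and FAMES". The factor being compared is fixed and the grouping unit is random.
- The Aim 3 models for repeated implementation measures have "random effects for sites and providers and fixed effects for time".

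**The concern.** Baseline, 3 months and follow-up are three chosen occasions, and the stated purpose is to compare scores between them. Because the analysis is confined to FAMES participants, time is its only contrast. A factor whose levels are themselves of interest is normally fixed, and the random effects go to the units that generate correlation, here participants and sites.

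If occasion is random, the three time points are treated as draws from a population of occasions and summarised by their variance. A reader of the results would want to know by how much, and in which direction, scores moved from baseline to 3 months, from baseline to follow-up, and from 3 months to follow-up. A variance has no sign and does not say which occasions differ. The same paragraph plans a Kenward-Roger correction, which serves inference on fixed effects. In a model without a fixed time effect it would have no time estimate to act on.

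**Working it through.** The article gives no sample size, effect size or power for this analysis, so there is no stated figure to reproduce. The check compares what the two specifications deliver from the same data.

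**Inputs from the article.** FAMES sample: 225 dyads (Family member and client participant dyads: "with 225 participant dyads to receive the ACC and 225 to receive FAMES"). Three occasions. Alpha 0.05 (Data analysis plan: "All quantitative analyses will utilize a type I error rate of *p* < 0.05").

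**Assumptions, not in the article.** Complete, balanced data; total SD 1; within-person correlation 0.5, so the residual variance is 0.5; mean shifts of 0.2 SD. Site is left out for simplicity.

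**1. Occasion random, crossed with participant.** The time parameter estimates the sum of squared deviations of the three occasion means, divided by 2.

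- Improvement (0, -0.2, -0.2): mean -0.133; squared deviations 0.0178 + 0.0044 + 0.0044 = 0.0267; variance 0.0133.
- Worsening (0, +0.2, +0.2): the same deviations with opposite sign; variance 0.0133.
- Transient change (0, -0.2, 0): mean -0.067; squared deviations 0.0044 + 0.0178 + 0.0044 = 0.0267; variance 0.0133.

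Simulation with 2,000 replicates gave mean variance components of 0.0134, 0.0128 and 0.0135. Three clinically different courses yield the same parameter.

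**2. Predicted occasion effects from that model.** The shrinkage factor is variance / (variance + residual/n) = 0.0133 / (0.0133 + 0.5/225) = 0.0133 / 0.0156 = 0.857. A true change of -0.20 is predicted as 0.857 × (-0.20) = -0.171; the simulated mean was -0.168. The sign survives, but the size is pulled towards zero and the quantity is not a fixed contrast.

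**3. Occasion fixed, participant random.** The 3-month minus baseline contrast has standard error √(2 × 0.5/225) = 0.067. Simulation recovered -0.20 under improvement and +0.20 under worsening, with an empirical standard error of about 0.067. Each change therefore has a signed estimate and an interval of about ±1.96 × 0.067 = ±0.13 SD.

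**4. Omnibus test.** In the balanced case, the exact test of zero time variance is F = MS(time)/MS(residual) on 2 and 2 × 224 = 448 degrees of freedom. This is the same statistic, with the same null distribution, as the fixed-effect test. The noncentrality is 225 × 0.0267/0.5 = 12, which gives power of about 0.88; simulation gave 0.88 to 0.89. A likelihood-ratio test of the variance rejected in 0.81 to 0.83 of the same runs. Either test detects that the means differ.

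**5. Occasion random within participant.** This is the other literal reading. In two simulated data sets with shifts of -0.3 and +0.3 SD, the fixed part was a single intercept (-0.158 and +0.275). The occasion variance came out equal to the residual variance (0.496 and 0.475), so the two were not separately identified. No change between occasions was estimated.

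**The case against.** The strongest reply is that the phrase is loose wording. The sentence describes a comparison of occasions and calls time a repeated measures factor. The paragraph plans Kenward-Roger inference, although it does not tie this expressly to the follow-up model, and Aim 3 shows that the authors know the usual specification. In a condensed article the words may stand for a mixed model with a participant random effect. That reading is plausible and nothing in the article rules it out. Equally, nothing states it: the sentence attaches the random effect to the factor being compared, and the next sentence lists only covariates as fixed. The same one-sentence correction is needed under either reading.

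A reader might infer something stronger: that the analysis is blind to change, or has no power. The documents do not support this. Zero time variance implies equal means, and in the balanced case the exact variance test is the fixed-effect F test. The predicted occasion effects also keep their sign. A claim of no power would need a Wald test of a three-level variance component, and the article names no such test.

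**Conclusion.** The point holds as a mis-specified sentence. As written, it replaces three signed changes with one unsigned variance from three levels, about 0.013 under each of the three patterns tried, and with predicted effects shrunken by about 14% (1 - 0.857). What is lost is direct estimation of the contrasts and their intervals, not the ability to detect that something changed. The figures rest on the assumed correlation of 0.5, shifts of 0.2 SD and complete data. The absence of fixed contrasts follows from the specification and does not depend on those values.

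The consequence is limited. This is a secondary, uncontrolled, FAMES-only analysis. A reader might infer that the primary engagement comparison or the baseline to 3-month change-score analysis is also compromised. The article specifies those separately, and the primary model has phase as a fixed effect.

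**What to change.** Reword the sentence so that occasion (baseline, 3 months, follow-up) is a fixed categorical effect, with random intercepts for participant and site. Report the baseline to 3-month, baseline to follow-up and 3-month to follow-up contrasts with Kenward-Roger confidence intervals.

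The cost is one sentence. No new data are needed, the wording then agrees with the Aim 3 models, and recruitment is expected to run to October 2029, so there is time.

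One separate matter can be settled in the same edit. Aim 1 describes follow-up outcomes as coming from FAMES participants alone, whereas Data collection procedures schedules follow-up in both conditions. If ACC follow-up data are included, the model also needs a fixed effect for condition and its interaction with occasion.

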**Methods:**

A stepped-wedge trial will be conducted with nine CSC sites, each randomized to one of three waves. CSC sites will initially recruit participant dyads into an attention control condition (*n* = 225) followed by a separate cohort of dyads who will receive FAMES (*n* = 225). Primary (engagement) and secondary (perceived stress, anxiety) outcomes, as well as mechanisms (self-efficacy, connectedness, motivation) among family members will be assessed. Secondary outcomes will also include client-level outcomes such as symptoms and engagement. Guided by the Reach, Effectiveness, Adoption, Implementation, Maintenance/Sustainability extension framework for sustainability, implementation outcomes (reach, adoption, implementation, sustainability) will be evaluated using mixed methods.

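### The Aim 1 Bonferroni family counts client attendance as primary, although Table 1 and the abstract make it secondary and the 0.025 used for power fits only the two family outcomes

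*Protocol article*

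**What the plan says.** Four places in the protocol article bear on the primary test for Aim 1.

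- **Table 1, primary outcome.** Engagement in family psychoeducation "will be measured as first session attendance rate and total attendance rate per family". That is two measures, both on the family.
- **Table 1, secondary client outcomes.** Client engagement "will be measured as the client attendance rate in CSC". That is one measure, listed as secondary. The abstract agrees: "Secondary outcomes will also include client-level outcomes such as symptoms and engagement".
- **Data analysis plan, Aim 1.** The multiplicity sentence reads: "A Bonferroni correction will be applied to primary engagement outcomes (first session attendance and total attendance per family and client) to control for multiple testing". It calls the set primary, includes the client, and gives neither the number of tests nor the adjusted level.
- **Power analysis.** Aim 1 power is computed "with an effect size of 0.5, at a 2-sided alpha level of 0.025", for 450 participants, and is said to be above 85%.

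The opening of the Data analysis plan also sets a general type I error rate of 0.05 for the quantitative analyses.

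**The concern.** Client attendance cannot be both a secondary outcome and a member of the primary Bonferroni family. The choice fixes the threshold for the trial's main claim, because Bonferroni divides 0.05 by the number of tests in the family. The power section has in effect divided by two, whereas the analysis section lists more than two outcomes on its plain reading.

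Two things are at stake. If the analysis sentence governs, family attendance is judged at a stricter level than the one the trial was powered for, and part of the error budget goes to a question that Table 1 does not call primary. If 0.025 is kept while the client outcome stays in the family, the correction no longer holds the family-wise error at 0.05. This is not a detail that the article has left to an analysis plan. The article does define the family, and its definition does not agree with its own outcome table.

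**Working it through.** **Inputs from the article.** Overall level 0.05 (Data analysis plan). Two family measures and one client measure (Table 1). Nine sites, three waves, N = 450, effect size 0.5, ICC 0.01, two-sided 0.025, power above 85% (Power analysis).

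**Step 1: per-test level by size of family.**

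- Two family outcomes: 0.05/2 = 0.025, the level in the power section.
- Two family outcomes plus client attendance: 0.05/3 = 0.0167.
- First-session and total attendance for family and client alike: 0.05/4 = 0.0125. This needs a client first-session measure, which Table 1 does not define.

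The p-values whose verdict depends on the section followed are therefore 0.0167 to 0.025 with three tests and 0.0125 to 0.025 with four.

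**Step 2: family-wise error if 0.025 is kept for every listed test.** The Bonferroni bound is 3 × 0.025 = 0.075 or 4 × 0.025 = 0.10. For independent tests it is 1 − 0.975³ = 0.073 or 1 − 0.975⁴ = 0.096.

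**Step 3: reproduce the stated power.** The article text does not give the period layout behind the calculation, so one must be assumed: a standard stepped wedge with three sequences of three sites, four periods, 450/36 = 12.5 participants per site-period, total SD 1, fixed period effects and a normal test. The generalized least squares variance of the effect is 0.02265, so SE = √0.02265 = 0.1505 and 0.5/0.1505 = 3.322.

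Power = Φ(3.322 − z(1−α/2)). At 0.025 this is Φ(3.322 − 2.241) = 86.0%, which agrees with the stated figure.

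**Step 4: change only the level.**

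| Tests in family | Level per test | z(1−α/2) | Power |
|---|---|---|---|
| 2 | 0.025 | 2.241 | 86.0% |
| 3 | 0.0167 | 2.394 | 82.3% |
| 4 | 0.0125 | 2.498 | 79.5% |

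**Step 5: dependence on the assumed layout.**

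- With 12 rather than 12.5 per site-period, power is 84.6%, 80.7% and about 78% for two, three and four tests.
- With a three-period wedge (450/27 = 16.7 per site-period) it is about 93%, 91% and 89%.
- With a parallel design effect of 1 + 24 × 0.01 = 1.24 or 1 + 49 × 0.01 = 1.49, it is 99.4% or 98.2% at 0.025, and 98.8% or 96.8% at 0.0125.
- With a t reference on 7 degrees of freedom in the four-period layout, it is about 68% at 0.025, so the match in step 3 also rests on the normal approximation.

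Of these, only the four-period layout with 12.5 per cell and a normal test gives a figure just above 85%. That makes it a plausible basis for the stated power but does not confirm it.

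**The case against.** The best defence is that the intended plan can be worked out. Table 1 gives two family outcomes, 0.05/2 is exactly the level used for power, and the words about the client could be a slip. On that reading nothing in the power section is wrong. This stands as far as it goes: the threshold is ambiguous, not wholly undefined. It does not remove the contradiction, because the analysis sentence explicitly places the client outcome in the primary set.

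Three stronger readings are tempting and not supported.

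- **The general 0.05 as a third, conflicting threshold.** A reader might take "All quantitative analyses will utilize a type I error rate of" 0.05 as a per-test level for the primaries, widen the disputed range to 0.05, and infer a family-wise error near 9.8% (1 − 0.95²). The sentence reads naturally as the overall level that the later Bonferroni sentence divides. No section proposes testing the primaries uncorrected.
- **Power overstated without qualification.** Under Table 1's two outcomes the assumed layout gives 86.0%, so the claim stands. With three tests, about 82% misses the 85% but still meets the section's closing claim of more than 80%. Only the four-test count falls below 80%, by half a point, and it rests on a client measure that Table 1 does not define.
- **Bonferroni as the wrong method.** It is valid. Holm would be no less powerful, but that is a preference and not a correction.

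**Conclusion.** The point holds as an inconsistency in wording that affects the primary threshold. The Aim 1 multiplicity sentence disagrees with Table 1 and the abstract on the status of client attendance, and with the power analysis on the number of tests. The disputed p-value range is 0.0167 to 0.025 for three tests, the better-supported count once the client is included, and 0.0125 to 0.025 for four. These ranges and the error bounds of 0.075 and 0.10 follow by arithmetic from the article.

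The power consequence is conditional. It arises only if the client outcome is counted, and its size (86.0% falling to about 82% or 79.5%) depends on an assumed layout. That the 0.025 for Aim 1 means two tests is itself an inference, since the power section does not explain the choice there. The matter should be corrected. It does not undermine the design.

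**What to change.** In the Aim 1 analysis section, remove the reference to the client from the Bonferroni sentence. State that the Aim 1 primary family is the two family-psychoeducation attendance outcomes, each tested at two-sided 0.025 for a family-wise level of 0.05, with client attendance secondary. Limit the statement to Aim 1, because Table 1 also lists engagement in FAMES (Aim 2) under the primary outcome. Holm at family-wise 0.05 may be used instead if the sponsor prefers.

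If client attendance is meant to be primary, amend Table 1 and the abstract to say so, name each client measure, state the divisor, and restate the power at 0.0167 or 0.0125.

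A clause in the opening of the Data analysis plan, saying that 0.05 is the family-wise level for the Aim 1 primary outcomes, would help as a clarification only.

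The first route costs wording alone and leaves the sample size and stated power unchanged. The second also needs the power calculation rerun. Recruitment is expected to run to October 2029, so either can be settled by a dated amendment before outcomes are compared between conditions.
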